### Design

A cluster-randomized controlled study design will be used, as IRS is a community-level intervention and the village cluster as a suitable unit for randomization. All households in all the clusters will be offered LLIN at no cost to the recipients to enable all residents to benefit from this intervention. The clusters will then be randomized into two equal groups; all households in the villages in one group will be offered IRS and those in the other group will not. It is not possible to conduct the IRS in a blinded manner since a placebo would quickly be identified by the community as non-protective. To assess whether DDT IRS and LLINs combined provide better protection against clinical malaria in children than LLINs alone, 75- 125 children aged from 6 months to 13 years old will be sampled according to cluster size enrolled into a study cohort. These children will be followed during the malaria transmission season in 2010 and 2011. Clinical malaria will be recorded by study staff using PCD in close collaboration with government health workers both at the village and health facility levels. Parasites will be detected by a rapid diagnostic test (RDT, Paracheck Pf, Orchid Biomedical Systems, Goa, India) and treatment will follow government treatment guidelines.

The study cohort will be surveyed for malaria indices (parasite prevalence, anaemia and spleen rate) at the end of both transmission seasons to generate data for the secondary endpoints and also at baseline before the year 1 transmission season. Baseline data will be used to compare the 2 groups before the interventions and end of season survey data will be used to attempt to define a *Plasmodium falciparum *parasitaemia cut-off giving optimum sensitivity and specificity for malaria cases in this setting [14].

Exposure to malaria vector mosquitoes and parasites indoors will be assessed using CDC light traps and window traps every 4 weeks from June to December and every 8 weeks from January to May in at least 6 randomly selected households in 16 village clusters in each arm of the study. This will be followed by detection of *Anopheles gambiae *species, parity status and sporozoite infection. A schematic representation of the trial is shown in Figure 1.

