### Randomisation

An equal number of clusters will be randomized to receive IRS, in addition to the LLINs provided to all enrolled households, and in these all households will be treated. In cluster-randomised controlled trials it is particularly important to minimize imbalance for factors known to be highly correlated with the disease outcome; in this case age and access to health facilities and location. At the village level we will stratify by presence of a primary health care centre (PHC) and geographical location by dividing the total area into four with two of equal area on each bank of the river. Stratification for PHCs will also ensure that the larger villages are evenly distributed in the experimental groups. In addition, balanced randomization will be used to ensure that children of similar ages are enrolled at the village level.

Stratified randomisation of villages to the study groups, as outlined above, will reduce the likelihood of chance imbalances between study arms but as only relatively small number of units can be randomized in such a cluster design, both groups cannot be assumed similar for all factors. Baseline data on spleen rates, parasite prevalence and anaemia will be collected on a representative sample of enrolled children in each village at the beginning of the main transmission season in 2010 to assess imbalances in malaria at village level.

Observer bias will be reduced where feasible. Blood films will be read by microscopists blinded to the identity and intervention status of the subjects. Mosquito collector bias will be reduced by using standard light traps and exit traps, which do not rely on the ability of the fieldworker to collect specimens. Trap catches will be examined by a different person to the trap collector and they will be blinded to the trap location. The processes of the interventions, both for LLINs and IRS, will be closely monitored not only for quality but also to document any bias between the villages.

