### Clinical evaluations

The main morbidity outcome will be incidence of clinical disease assessed by PCD; data from this will provide the primary endpoint of the study. PCD is considered to generate information of more direct relevance to public health than active case detection and is thus more suitable for evaluating population level malaria interventions [16]. Mild malaria and parasitaemia is common in all children in this area of highly seasonal malaria [17,18] and we will enrol children aged 6 months - 13 years. We previously developed a system in Gambian villages where a trained MRC nurse provided diagnostic support to the established VHW in the study villages [19]. Following this experience, in this study the nurses will provide training and ongoing support to the VHW for diagnosis of malaria in consulting study children who report with a history of fever in the last two days using RDT and treatment of malaria. Study nurses at the health facilities will document episodes of malaria in study children who present directly to them on the Case Report Form (CRF). At the health facilities malaria diagnosis will also rely on the use of RDT but, in addition, thick blood films will be made for later staining with Giemsa and microscopy to estimate parasite density in this subset of cases. To facilitate documentation of all clinical events (i.e. clinical consultations by study children), all enrolled children will be issued with enumerated photo identity cards; the study number and village will be recorded for all clinical events on the CRF. The project field workers or nurses that visit each VHW will complete the CRF for all study subjects that consult with the VHW.

All children present in their villages at the surveys will be clinically examined for obvious symptoms and signs of illness, temperature and spleen enlargement. A sample of all the study children, at least 50/village cluster will be randomly selected stratified by age, and these as well as those reporting fever in the last 48 hours and/or with a temperature of ≥37.5°C will be finger pricked for immediate measurement of anaemia and presence of parasites by RDT. Anaemia will be assessed by measuring haemoglobin concentration using a spectrophotometer (HaemoCue^®^) in the field.

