### Sample Size Rationale

#### a) Clinical

Both LLINs and IRS alone reduce malaria morbidity by approximately 50% [5,6]. The combined impact of these two interventions is unknown. If the effects were simply additive a mean reduction of 75% could be anticipated for the combination, but the effects may be synergistic (e.g. by having a mass killing effect) or antagonistic (e.g. the repellency of DDT reducing *Anopheline *house entry and contact with LLINs). To cover these possibilities we expect that LLINs will reduce incidence by 50%, with LLINs and IRS combined reducing the residual incidence by 30-60% (i.e. 50% vs 65-80% fewer clinical cases of malaria). A study of 3-60 month old children during the end of the rainy season (Sept-Dec) in the URR in 2007 found a seasonal incidence of 0.79 (95% CI: 0.58-1.08) cases/child-years by PCD ([name] pers. comm.); ITN prevalence was 50%. We estimate conservatively that increasing LLIN provision to > 80% and inclusion of older children will reduce incidence rates by about 60-80%, so incidence rates of 0.30 (LLINs) to 0.15 cases/child-years (LLINs & IRS) have been included in the sample size estimations. The study will also record PCD over two high transmission seasons, not 1 as in the [name] study, further enhancing our ability to detect differences between study arms. Estimations for k, the corrected coefficient of variation to adjust for between cluster variation (based on within and between cluster variation) [27], from a cluster trial conducted in the Central River Region of The Gambia in 2006/7 ([name] personal communication) varied from 0.31-0.43 and has been used to explore sample sizes (Figure 2). Two of the 5 districts in URR have 70 villages suitable for the trial with over 100 children aged 6 months-14 years (predicted from the 2003 National Census) and could accommodate an average cluster size of 110 children (range 75-125). We plan to follow these children for 22 weeks covering the peak malaria incidence season each year, which, allowing for a 20% drop out rate over the 2 years, yields 74.4 child-years per cluster. The graphs below indicate a sample size of 5-39 clusters per arm (Figure 2). Since estimates for incidence and drop-out rate are conservative and the value of k may also be reduced by the stratified design, we will recruit 35 clusters in each arm of the trial.

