### Analytical plan

#### Outcome 1 - malaria morbidity

The primary endpoint is a comparison of the incidence of clinical episodes of malaria in children in the 2 intervention groups, measured by PCD. After a case of malaria is treated, time of observation will be censored for 3 weeks and further attacks of malaria during this period are not considered. History of travel away from the village for prolonged periods will be captured by monthly surveys and time at risk will be censored for such periods. In addition, malaria cases in children who resided outside their study village for more than half the elapsed study period at the time of illness will be censored. An initial unadjusted analysis will be based on comparisons of the incidence rates between the 2 groups. Incidence rates will be calculated for each cluster and the ratio of their un-weighted means will give an estimate of the intervention effects. Confidence intervals for the intervention effect will be obtained using the approximations given by Bennett [29] and tested using a bootstrapped [30] confidence interval. The incidence rates for each cluster will also be used to perform a hypothesis test based analysis between the 2 groups using a 2 sample unpaired t-test. It is likely that the rates will be highly skewed and if necessary the rates will be transformed. Using the incidence rates as a response, linear regression can be used to adjust for cluster level covariate effects. If the assumptions of normality and constant variance cannot be met, a non-parametric test (Mann-Whitney) will be used to compare the 2 groups. The cluster randomised trial will result in a multi-level model with individuals within village. Individual level covariates will be modelled using random effects Poisson regression which will be fitted using GLLAMM, a Stata program to fit generalized linear latent and mixed models GLLAMM [31], to allow for the clustering effect of village, compound and the effect of repeated episodes in the same child. Year will be included as a fixed effect which will allow any interaction with the intervention to be quantified. Other potential confounders such as house architecture, bednet use and recent antimalarial treatment will also be adjusted for in the analysis. Should the data, be zero-inflated or under/over dispersed modifications to the underlying distributional assumptions will be examined. The time to first infection will be examined using a survival analysis approach. Initial unadjusted analysis will use Kaplan Meier curves to compare the probability of subjects in the two arms becoming infected as the malaria season progresses. A Cox regression frailty model will be used to adjust for covariates, allowing for the clustering. The location of the infected subjects will be known to the household level and this information will be used to examine the spatial distribution of infection over time. Within the larger villages formal methods such as k-means fuzzy clustering [32] will be used to quantify clusters of infection.

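### Village baseline malaria is collected but not named as a covariate for the primary incidence comparison; if it truly precedes the interventions, it should be pre-specified

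*Protocol article*

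**What the plan says.** **Baseline survey.** Under Randomisation: "Baseline data on spleen rates, parasite prevalence and anaemia will be collected on a representative sample of enrolled children in each village". The purpose given there is to assess village-level imbalance in malaria. Under Design: "Baseline data will be used to compare the 2 groups before the interventions". Under Clinical evaluations, the finger-prick sample at the surveys is defined: "A sample of all the study children, at least 50/village cluster will be randomly selected stratified by age".

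**Primary incidence analysis** (Analytical plan, Outcome 1). The estimate is crude: "Incidence rates will be calculated for each cluster and the ratio of their un-weighted means will give an estimate of the intervention effects". The cluster rates are then used to "perform a hypothesis test based analysis between the 2 groups using a 2 sample unpaired t-test", with a rank test as fallback. Cluster-level adjustment is permissive: "Using the incidence rates as a response, linear regression can be used to adjust for cluster level covariate effects". After the random effects Poisson model is introduced, the article adds: "Other potential confounders such as house architecture, bednet use and recent antimalarial treatment will also be adjusted for in the analysis". Baseline malaria is not in that list.

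**The concern.** Villages differ in malaria, and this between-village variation is a large part of the noise when 35 villages are compared with 35. The baseline survey is the one measure of village malaria that the plan describes as taken before the interventions. The article gives it a descriptive role, while one of the covariates it does name, bednet use, is recorded in mid-season after the interventions. If the baseline value predicts incidence, leaving it out of the main comparison gives up precision already paid for. This matters most where the sample size is tightest: the article's own range reaches 39 clusters per arm and 35 are recruited. Leaving adjustment optional, with covariates unnamed, also leaves open which estimate will be treated as the main one.

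**Working it through.** **Inputs from Sample Size Rationale, a) Clinical:** 35 clusters per arm; 110 children per cluster; 22 weeks in each of 2 years; 20% drop-out; 74.4 child-years per cluster; k from 0.31 to 0.43; reduction 30-60%; and "incidence rates of 0.30 (LLINs) to 0.15 cases/child-years (LLINs & IRS) have been included in the sample size estimations".

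**Assumptions:** two-sided 5% and 80% power, since the text states these only for secondary endpoints; 0.15 and 0.30 read as the two ends of the control rate. Step 2 supports both.

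**1. Child-years.** 110 × 22/52 × 2 × 0.8 = 74.46, in agreement with 74.4.

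**2. The plan's cluster range.** For unmatched cluster rates,

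c = 1 + (1.96 + 0.84)² × [(λ0 + λ1)/y + k²(λ0² + λ1²)] / (λ0 − λ1)², with y = 74.4 and (1.96 + 0.84)² = 7.849 from unrounded values.

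- λ0 = 0.15, λ1 = 0.105, k = 0.43: 1 + 7.849 × (0.003427 + 0.006199)/0.002025 = 38.3, so 39.
- λ0 = 0.30, λ1 = 0.12, k = 0.31: 1 + 7.849 × (0.005645 + 0.010033)/0.0324 = 4.8, so 5.

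This is the article's 5-39. At 90% power the range would be 7-51, so 80% was used.

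**3. Unadjusted power with 35 clusters, least favourable case.** √(34 × 0.002025/0.009626) = 2.674; Φ(2.674 − 1.96) ≈ 76%.

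**4. Room for a covariate to help.** Between-village variation is 0.006199/0.009626 = 64% of the variance here, and 48-78% over the four 30%-reduction scenarios.

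**5. Adjusted power.** Replace k² by k²(1 − r²), where r is the correlation of measured baseline prevalence with the true between-village part of incidence. The article gives no r, so a range is shown. Example for r = 0.5: 0.003427 + 0.75 × 0.006199 = 0.008077; √(34 × 0.002025/0.008077) = 2.920; power 83.1%.

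| Control rate | k | r = 0 | r = 0.3 | r = 0.5 |
|---|---|---|---|---|
| 0.15 | 0.43 | 76% | 78.7% | 83.1% |
| 0.30 | 0.43 | 83.9% | 86.4% | 90.8% |
| 0.15 | 0.31 | 89.6% | 90.8% | 93.0% |
| 0.30 | 0.31 | 96.2% | 97.1% | 98.3% |

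All rows are for a 30% reduction. In the first row, the clusters per arm needed for 80% power fall from 39 to 37 and 33. At a 40% reduction, unadjusted power is 96% or more in all four combinations.

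**6. Sampling noise.** With 50 children per village, the reliability of measured prevalence p is (kp)²/[(kp)² + p(1 − p)/50]. For assumed p of 5%, 10% and 20% this is 0.33, 0.51 and 0.70 at k = 0.43, and 0.20, 0.35 and 0.55 at k = 0.31 (assuming prevalence varies between villages with the same k). If *true* village prevalence correlates 0.5 with true village incidence, then r = 0.5 × √reliability = 0.29-0.42 at k = 0.43, and power in the least favourable case is about 78-81%.

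**7. Timing, side by side.** Design places the survey before the interventions. Study procedures and evaluations intends spraying and nets to be finished in May. Study area and participant eligibility puts enrolment in June 2010. Table 1 shows spraying and nets in May and June and the first clinical survey in June. These do not establish that the survey comes first in each village.

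**The case against.** The strongest reply is that nothing is excluded. The crude comparison is labelled an initial analysis, cluster-level regression is foreseen, the covariate list is introduced by examples, and a statistical analysis plan that is not shown may name baseline prevalence. This stands against any claim that the survey is barred from the primary analysis: the covariate is unnamed, not ruled out. It does not answer the narrower point that the article fixes the estimate and test as unadjusted and gives the baseline survey another job.

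A reader might also infer that the investigators will look for imbalance and then decide whether to adjust. The article states no such rule; it says only that imbalance will be assessed.

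A reader might infer that adjustment would restore the power at no cost. That is not supported either. No correlation or baseline prevalence is given, the survey precedes a highly seasonal transmission period and would have to predict two seasons, and about 50 children per village measure prevalence imprecisely. The shortfall below 80% lies at the low-rate, high-k, small-effect end, and the article hopes stratification will lower k, which the calculation above does not credit.

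The timing objection stands in full: adjusting for a survey taken after spraying could absorb part of the effect.

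**Conclusion.** The point holds in limited form. The stated uses of the village baseline survey are descriptive, the primary estimate and test are unadjusted, and baseline malaria is not among the named covariates. Pre-specifying it is a better use of data already collected. In the least favourable planned case the gain is from about 76% to about 79-83% power for r of 0.3-0.5, and less once sampling noise is allowed for. It is about 1 to 3 points at k = 0.31 and negligible at effects of 40% or more. These figures rest on an assumed correlation, the normal approximation used for the sample size, and no credit for stratification. The recommendation is conditional on the survey preceding both interventions in each village.

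**What to change.** 1. First reconcile Design, Study area and participant eligibility, Study procedures and evaluations, and Table 1 on whether the 2010 baseline survey precedes spraying and net distribution in each village. If it does not, this covariate should not be used.
2. If it does, state under Outcome 1 that village baseline P. falciparum prevalence is a fixed covariate, with its scale given in advance, in both the cluster-level regression of (log) incidence rates and the random effects Poisson model.
3. Make the adjusted cluster-level estimate the main one and report the unadjusted ratio and t-test as supportive. On the log scale the effect is a ratio of geometric means, which should be said.
4. Use the village value, not the child's own, so that children recruited in year 2 are covered.

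Cost: a short addition to the text, one regression term, no new data, and one degree of freedom out of 68 (70 clusters less 2 arm means).

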### Interventions

#### a) Indoor-residual spraying

In study clusters randomized to IRS, indoor residual spraying will use a wettable powder of DDT (DDT- WP 75) manufactured to WHO specifications and supplied by Hindustan Insecticide Ltd., New Delhi, India. Indoor surfaces will receive DDT (2 g/m^2^), in May/June, at the start of the main malaria transmission season, in 2010 and 2011. DDT-WP 75, contains 500g of DDT per 670g of product and is packaged in 670g/sachets for making up to 10L with water. The sachets are clearly labelled following WHOPES guidelines (WHO/CDS/WHOPES/2003.7) and are delivered 25/heavy duty carton.

DDT will be stored to maintain efficacy and avoid environmental contamination according to WHOPES guidelines (WHO/CDS/WHOPES/2003.7) and in accordance with the Gambian National Environmental Agency's regulations. Thus the study DDT will be stored in a similar manner to DDT being used currently by the NMCP. The cartons containing individual sachets will be clearly marked with the study name (SANTE) and stored in a locked designated area in the Central Medical Stores until the week before the IRS campaign, each year, when they will be moved to a locked designated area at the Regional Store in Basse. While in the Central and Regional Stores the DDT will be under the control of the NMCP Study Investigators, who will supervise the interventions. The product will be supplied with an expiry date 2-years post-manufacture which will extend beyond June 2011.

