#### b) Long-lasting insecticidal mosquito nets

LLINs distributed during this project will be Olyset Nets, Sumitomo Chemicals. These meet WHO specifications (http://www.who.int/whopes/Long_lasting_insecticidal_nets_Aug09.pdf) with permethrin at 2% w/w incorporated into polyethylene fibres giving adequate release of permethrin for up to five years. Recipients will be offered a choice between the "large" conical (1250 cm circumference, 65 cm top, 250 cm high) and the "family" rectangular (160 cm wide × 180 cm l × 150 cm h) models. Olyset nets are supplied in individual sachets labelled by the manufacturers and they will be distributed to recipients in pre-opened individual sachets in May 2010, at the beginning of the main transmission season.

Olyset LLIN will be stored at ambient temperature in locked rooms in Banjul and Basse and will be under the control of the NMCP Study Investigators. LLIN distribution will conducted in collaboration with the Regional Government bednet distributors at no cost to the recipients. In advance of distribution, the number of beds/sleeping places and the number with LLIN in excellent condition will be counted. Distribution will be at the household level to the household head or representative to achieve one LLIN per bed/sleeping place. Net use by study children will be monitored during the middle of the transmission season in 2010 and 2011. Government Roll Back Malaria information, education and communication procedures will be followed to encourage correct net use and maintenance.

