### Study procedures and evaluations

In advance of the spray campaign in year 1, spray operatives and supervisors will be trained on the WHO methods for IRS with DDT for two weeks by the NMCP vector control officer seconded to the project and an internationally recognized IRS consultant. They will be equipped with personnel protective clothing, including boots, long-sleeved cotton overalls, hat, gloves, mask and boots and trained in the maintenance and use of these. Spray operatives will use spray pressurized canisters made to WHO specifications WHO/VBC/89.970 (Hudson X-Pert^® ^Sprayer, 15L model 67422AD with stainless steel nozzle (8002E), flat fan pattern, 80° angle, flow rate 0.76L/min at 45psi pressure). They will be rigorously trained in the use of these and their maintenance. A 2-day refresher training will be provided before the spray campaign in year 2. Any remnant in the sprayers at the end of daily spraying will be collected following the "Progressive Rinse" method and recycled to minimize waste (http://www.hdhudson.com/global-public-health/newsletters/technical-information accessed 9th June 2011).

It is intended that both IRS and LLIN distribution will be completed in May both years. In year 2 all households in the arm randomized to this intervention will receive IRS as in year 1. LLIN distribution in year 2 will be to residents who have relocated to study villages since year 1.

Village health workers will be provided with refresher training on diagnosis of malaria, the use of RDT and study procedures in July 2010 by the study physician in collaboration with study nurses and the community health nurses. The methods used will be informed by ongoing studies in The Gambia on the introduction of RDT at all levels of health service. Refresher training will be provided in 2011 before the transmission season.

Movement of children will be assessed at monthly intervals on brief questionnaires to estimate the time at risk and bednet usage will be assessed during these house visits in August each year.

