#### Secondary endpoints

For the secondary clinical endpoints we will compare: (i) mean haemoglobin concentration in children at the end of the transmission season, (ii) incidence of malaria defined by history of fever or temperature of ≥37.5°C and a *P. falciparum *parasitaemia cut-off defined to give optimum sensitivity and specificity in this setting, (iii) parasite prevalence in children at the end of the transmission season, (iv) number of children with enlarged spleens at the end of the transmission season. In general, all quantitative outcomes will be compared using appropriate summary statistics, such as mean differences or risk ratios. Hypothesis testing will be based on a two sample unpaired t-test, adjusting for possible co-variates. If the data do not satisfy normality and constant variance assumptions, an appropriate non-parametric test will be used. Both linear regression (for continuous variables such as haemoglobin levels) and logistic regression (for dichotomous variables such as presence or absence of parasitaemia) will be used to quantify the group differences allowing for individual level covariates (such as age, house design, bed net use) using random effects to allow for clustering.

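### The child-level effect models adjust for net use and recent antimalarial treatment, which can arise after randomisation, so the adjusted IRS estimates can be biased for the total effect of adding IRS to LLINs

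*Protocol article*

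**What the plan says.** The primary endpoint is analysed in two layers (Analytical plan, Outcome 1). The first is at cluster level: "An initial unadjusted analysis will be based on comparisons of the incidence rates between the 2 groups". It gives a ratio of mean cluster rates, a confidence interval and a t-test. The second is at child level: "Individual level covariates will be modelled using random effects Poisson regression which will be fitted using GLLAMM". On covariates, the same paragraph says: "Other potential confounders such as house architecture, bednet use and recent antimalarial treatment will also be adjusted for in the analysis". The section on secondary endpoints uses regression to quantify the group differences, "allowing for individual level covariates (such as age, house design, bed net use" being its examples.

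The timing is given elsewhere:

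- Spraying takes place "in May/June, at the start of the main malaria transmission season, in 2010 and 2011" (Indoor-residual spraying).
- "Net use by study children will be monitored during the middle of the transmission season in 2010 and 2011" (Long-lasting insecticidal mosquito nets).
- "bednet usage will be assessed during these house visits in August each year" (Study procedures and evaluations).
- On blinding: "It is not possible to conduct the IRS in a blinded manner" (Design).

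Detected malaria is treated, and children may also receive medicines from outside the study team (Clinical data collection and patient treatments). The look-back period for recent treatment is not defined. The article neither limits these two covariates to values from before the intervention nor labels the models exploratory.

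**The concern.** Randomisation already removes confounding in expectation, so a variable that allocation can change is not a confounder of the arm comparison.

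**Net use.** Families know whether their house was sprayed, and the entomological sample-size section expects DDT to deter 60-70% of mosquitoes from entering. Fewer mosquitoes indoors could change how often nets are used. Net use would then lie on the path from IRS to malaria, and adjusting for it removes that part of the effect.

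**Antimalarial treatment.** Children with malaria are treated. If IRS prevents malaria, it also reduces treatment, so the covariate partly records earlier endpoint events. The model counts repeated episodes, so treatment of one can become a predictor of the next.

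The protocol wants to inform policy on the marginal benefit of adding IRS where LLINs are best practice. That is a total effect, including any change in net use. The adjusted model targets something else, and could disagree with the unadjusted comparison for that reason alone.

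**Working it through.** **Reproducing the plan's figures.** Child-years per cluster: 110 x 22/52 x 2 x 0.8 = 74.46 (stated 74.4). Clusters per arm, by the standard formula for rates in an unmatched cluster trial, with y = 74.4 and assuming two-sided 5% and 80% power:

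c = 1 + (z_a + z_b)^2 x [(r0 + r1)/y + k^2(r0^2 + r1^2)] / (r0 - r1)^2

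- r0 = 0.30, 60% reduction, k = 0.31: 4.8, rounded up to 5.
- r0 = 0.15, 30% reduction, k = 0.43: 38.3, rounded up to 39.

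This matches the stated 5-39. The point below does not alter the sample size.

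**Net use: arithmetic.** From the protocol: a net halves incidence (Background), LLIN provision is about 80%, and the smallest planned effect is a 30% reduction, a ratio of 0.70 (Sample Size Rationale). Assumed: provision stands for use, 0.70 is the effect at fixed net use, and IRS lowers use by d.

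Total ratio = direct ratio x [(1 - p1) + 0.5 p1] / [(1 - p0) + 0.5 p0], with p0 = 0.8 and p1 = 0.8 - d.

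| d | Total ratio | Net-adjusted ratio |
|---|---|---|
| 0 | 0.70 x 0.60/0.60 = 0.70 | 0.70 |
| 10 points | 0.70 x 0.65/0.60 = 0.76 | 0.70 |
| 20 points | 0.70 x 0.70/0.60 = 0.82 | 0.70 |

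With no direct effect and a 20-point fall, the total ratio is 1.00 x 0.70/0.60 = 1.17, while a net-adjusted model targets 1.00. If IRS raised net use, the error would run the other way.

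**Net use: simulation.** Settings: 35 clusters per arm, 110 children each, control rate 0.30, k = 0.37, child-level frailty variance 0.8, one 22-week season in two halves, plain Poisson regression, 60 runs. Net-adjusted ratios with a direct ratio of 0.70 were 0.70 to 0.71 for d = 0, 10 and 20 points. With no direct effect and d = 20 points, the net-adjusted ratio was 1.03 over 60 runs and 1.01 over 300, so the excess over 1.00 is simulation noise.

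**Antimalarial treatment: simulation.** The size depends on coding.

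- Treatment in the preceding half-season only (settings above): 0.70 becomes 0.72, and 0.50 becomes 0.52.
- Any treatment in the season, including that of the counted episode (cluster CV 0.35, frailty variance 1, 10% background treatment): 0.70 becomes about 0.81, and 0.50 about 0.65. A rerun with 100 replicates gave 0.82 and 0.66.

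**Scale.** With rates 0.30 and 0.21, k = 0.37 and 35 clusters per arm, the standard error of the log rate ratio is sqrt{[1/(0.30 x 74.4) + 1/(0.21 x 74.4) + 2 x 0.37^2]/35} = 0.105. The shift from 0.70 to 0.72 is ln(0.72/0.70)/0.105 = 0.27 standard errors. The gap between 0.70 and 0.82 is ln(0.82/0.70)/0.105 = 1.5 standard errors.

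**The case against.** A reader might infer that the trial's main result is biased. The documents do not support that. The unadjusted cluster-level comparison comes first, contains neither covariate and estimates the total effect. Nothing makes the Poisson model decisive.

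Bias through net use is also conditional. It requires IRS to change net use, and the documents give no sign of how much, if at all. Free nets for every sleeping place and education on their use in both arms favour similar use. A reader might likewise take the shift from 0.70 to about 0.81 as the expected effect of adjusting for treatment. That needs a coding which includes treatment of the counted episode. The word recent points to earlier treatment, where the shift is small, and the plan censors three weeks after each treated case. The simulations also lack the planned random effects, so they only illustrate.

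Finally, the covariates are introduced as examples, a fuller analysis plan may exist, and a supportive analysis allowing for actual net use is reasonable.

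Most of this stands and limits the size. It does not remove the point. The article commits to these two covariates by name, calls them confounders, does not say which estimate is decisive, and repeats the net-use adjustment where it quantifies differences on secondary endpoints. Table 1 marks a clinical and bednet survey in June 2010, but spraying is marked in May and June, and the text puts monitoring of children's net use mid-season. House architecture is not part of the problem.

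**Conclusion.** The concern holds in a limited form. The child-level model for the primary endpoint and the secondary-endpoint regressions are set to adjust for variables that allocation or the outcome can change. Their estimates can therefore be biased for the total effect of adding IRS to LLINs.

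The size cannot be known from the documents. It is nil through net use if IRS leaves use unchanged. It is 0.06 to 0.12 on the rate ratio for an assumed 10 to 20 point fall with nets halving risk. It is about 0.02 through earlier treatment, and about 0.11 (at a true 0.70) to 0.15 (at 0.50) if treatment of the counted episode is included. The unadjusted comparison stands, so this is a correction to the adjusted analyses and not a threat to the trial's basic result. That treatment is recorded after randomisation is inferred from treatment during follow-up, because recent is not defined.

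**What to change.** In Outcome 1 and the secondary-endpoint section:

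1. Restrict covariates in the effect models to the stratification factors (PHC presence and geographical area) and variables measured before the intervention. Examples are age, house construction, the household net count taken before distribution, and baseline cluster prevalence where that survey preceded spraying.
2. Name the unadjusted or baseline-adjusted estimate as the effect estimate.
3. Report mid-season net use and antimalarial treatment by arm. Put any model containing them under a clear exploratory label, with the look-back period for recent treatment defined so that treatment of the counted episode is excluded.

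This costs a few sentences, needs no new data and leaves the sample size unchanged. It should be settled before the data are analysed.
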